## Abstract

**Background:**

Low back pain, radicular symptoms, and functional impairment are common manifestations of lumbar disc herniation (LDH), which can substantially impair patients' quality of life. Tuina therapy and core stability training are widely used conservative interventions for LDH, often applied as a combination of passive manual therapy and active exercise to alleviate symptoms and improve function. However, most existing clinical studies are limited by small sample sizes and methodological weaknesses, and robust evidence is lacking regarding whether the combined intervention is superior to either therapy alone.

**Methods:**

This study is a single-center, outcome assessor- and data analyst-blinded, randomized controlled trial. A total of 96 patients with LDH will be randomly allocated in a 1:1:1 ratio to the Tuina group, the core stability training group, or the combined intervention group. All participants will receive an 8-week intervention (three sessions per week), followed by a 1-month follow-up period. The primary outcome is the muscle activation ratio of the transversus abdominis assessed by musculoskeletal ultrasound. Secondary outcomes include imaging parameters, pressure biofeedback unit (PBU), the Visual Analog Scale (VAS), the Oswestry Disability Index (ODI), the Japanese Orthopedic Association (JOA) score, and the 36-Item Short Form Health Survey (SF-36). Objective outcomes (musculoskeletal ultrasound, MRI, X-ray, PBU) will be assessed by researchers blinded to group allocation. Patient-reported outcomes (VAS, ODI, JOA, and SF-36) are inherently unblinded as participants are aware of their treatment assignment. Statistical analysis will be performed without knowledge of group allocation.

**Conclusion:**

This study is expected to provide high-quality evidence on the efficacy and safety of Tuina combined with core stability training in improving lumbar stability and clinical outcomes in patients with LDH.

**Clinical trial registration:**

International Traditional Medicine Clinical Trial Registry (ITMCTR, http://itmctr.ccebtcm.org.cn/), identifier: ITMCTR2025001794.

## Introduction

1

Lumbar disc herniation (LDH) is a common musculoskeletal disorder caused by degenerative changes in the intervertebral disc, resulting in protrusion or extrusion of the nucleus pulposus that compresses or irritates adjacent nerve roots. It typically presents with low back pain, radiating leg pain, and functional impairment (1). The prevalence of LDH in China ranges from 8% to 25%, making it one of the leading causes of low back pain (2). In recent years, the incidence of LDH has shown an increasing trend with a younger age of onset, most commonly between 30 and 55 years.Some studies suggest a higher incidence in men than in women. Approximately 95% of cases occur in the lower lumbar spine, particularly at the L4/5 and L5/S1 levels (3). Clinical manifestations range from isolated low back pain to severe neurological deficits such as cauda equina syndrome (4). These conditions substantially impair quality of life and impose a significant socioeconomic burden. Currently, the management of LDH can be broadly categorized into surgical and nonsurgical approaches. Given considerations of effectiveness and safety, nonsurgical treatments are generally recommended as the first-line option for most patients (5). Conservative strategies include pharmacological therapy, manual therapy, and exercise-based rehabilitation. Although medications can effectively relieve pain, they are often associated with adverse effects and have limited impact on restoring lumbar stability and functional capacity (6).

The pathogenesis of LDH is closely associated with intervertebral disc degeneration, reduced water content of the nucleus pulposus, narrowing of the intervertebral space, and decreased lumbar stability (7). Degenerative changes disrupt the biomechanical balance of the lumbar spine, leading to spinal instability (8). In turn, impaired stability further accelerates disc degeneration, forming a self-perpetuating cycle. In this context, the lumbar–abdominal musculature plays a critical compensatory role in maintaining spinal stability by distributing mechanical loads and supporting both static alignment and dynamic control (9). Therefore, restoring lumbar stability, particularly through improving neuromuscular function of the core musculature, has become a key therapeutic target in the conservative management of LDH (10).

Current clinical practice guidelines recommend Tuina therapy and exercise-based rehabilitation as important nonsurgical interventions for LDH (6, 11). Tuina, a traditional manual therapy, has been shown to relieve pain and improve functional outcomes, potentially through mechanisms such as enhancing local circulation, reducing inflammation, and modulating neural activity (12). The Tuina protocol applied in this study primarily targets the Dai meridian region, which anatomically corresponds to the lumbar–abdominal musculature and thoracolumbar fascia. Acupoints such as Daimai (GB26), Wushu (GB27), and Weidao (GB28) are anatomically located along the lateral abdominal wall, corresponding to the external oblique, internal oblique, and transversus abdominis muscle layers. These points have been widely selected in clinical and experimental studies based on their relevance to abdominal musculature and their role in modulating lumbar stability and core function (13).Previous studies from our research group have demonstrated that abdominal Tuina can increase transversus abdominis thickness and improve lumbar function (14, 15). However, existing evidence suggests that while Tuina is effective in alleviating pain and improving physical function, its effects are primarily limited to symptomatic relief, with insufficient influence on deep muscle activation and neuromuscular control, which are essential for long-term spinal stability (9, 16).

Core stability training, as a representative form of exercise-based rehabilitation, directly targets the neuromuscular mechanisms underlying spinal stability. It aims to improve coordination and activation of deep stabilizing muscles, thereby enhancing spinal and pelvic stability. By strengthening these muscles, core stability training can reduce excessive loading on superficial lumbar structures and address instability caused by muscle imbalance or fatigue (17, 18). Previous studies have demonstrated that core stability training can significantly reduce pain and improve functional performance in patients with LDH (19, 20). Nevertheless, exercise-based interventions alone may have limited effects on soft tissue relaxation and pain modulation, particularly in the early stages of treatment. Given their distinct yet complementary mechanisms, Tuina therapy and core stability training may exert synergistic effects in the management of LDH. Tuina primarily improves soft tissue condition and alleviates pain, whereas core stability training enhances neuromuscular control and spinal stability. However, current evidence remains insufficient to determine whether the combined intervention is more effective than either therapy alone, particularly in improving lumbar stability and related clinical outcomes.

Consequently, the present study proposes to conduct a randomized controlled clinical trial with blinded outcome assessment and data analysis to further validate the effectiveness of the combined intervention. A combination of musculoskeletal ultrasound, imaging assessments, pressure biofeedback unit assessment, and patient-reported outcome measures will be used to comprehensively evaluate lumbar stability and clinical outcomes. This approach will help determine whether the combined therapy provides superior benefits compared with single interventions.

## Methods

2

### Study design

2.1

This study is a single-center, three-arm parallel explanatory randomized controlled trial conducted in China (Figure 1). A total of 96 patients with LDH will be recruited and randomly allocated in a 1:1:1 ratio to the Tuina group, the core stability training group, or the combined intervention group. Participants who meet the inclusion criteria will be enrolled after providing written informed consent. Participants will be recruited from 15 October 2025 to 1 November 2027 through outpatient clinics, public advertisements, and social media platforms. All three groups will receive an 8-week intervention, administered three times per week, followed by a 1-month follow-up period. Outcome assessments will be conducted at baseline, after 8 weeks of intervention, and at the end of the follow-up period. The intervention duration was determined based on dose–response evidence, direct clinical trials, and prior rehabilitation literature. A recent systematic review and meta-analysis on stabilization-based exercise in patients with chronic low back pain reported that 8–12-week interventions produced the greatest effects on pain reduction (SMD = –0.88) and disability improvement (SMD = –0.85), with high-certainty evidence for disability outcomes (21). Consistent with this evidence, randomized controlled trials in patients with LDH have commonly adopted 8-week core stabilization protocols. An 8-week motor control training program significantly improved pain, disability, and transversus abdominis activation (22), while an 8-week program (three sessions per week) also demonstrated significant improvements in pain, disability, and trunk muscle endurance (23). Accordingly, an 8-week intervention period was selected, representing a commonly adopted duration within the evidence-supported 8–12-week therapeutic window for stabilization-based interventions in LDH. A 1-month follow-up assessment was included to evaluate the short-term maintenance of treatment effects after completion of the intervention, which is consistent with early post-intervention assessment time points used in randomized controlled trials of LDH (24). To enhance methodological rigor and minimize potential bias, blinded outcome assessment and statistical analysis procedures were incorporated into the study design. Outcome assessment and statistical analysis will be performed by two independent researchers who are blinded to group allocation. The primary and secondary outcome measures include musculoskeletal ultrasound, imaging assessments, pressure biofeedback unit assessment, and patient-reported clinical outcomes to comprehensively assess lumbar stability, pain, and functional status. The study protocol was developed in accordance with the SPIRIT guidelines, and the completed SPIRIT checklist is provided as Supplementary Table S1. In addition, a treatment fidelity checklist is provided as Supplementary Table S2 to ensure consistency and quality of intervention delivery.

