### Outcomes

2.7

The efficacy evaluation in this study will focus on the primary and secondary outcome measures assessed at baseline and immediately after the intervention. In addition, selected clinical outcomes, including pain intensity and functional status, will be reassessed at the 1-month follow-up using the VAS and ODI to evaluate the persistence of treatment effects. Follow-up assessments will be conducted by independent outcome assessors who are blinded to group allocation.All outcome assessments will be conducted by independent researchers who are blinded to group allocation and are not involved in other aspects of the study. The schedule of enrolment, interventions, and assessments is presented in (Figure 5).

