##### Musculoskeletal ultrasound assessment

2.7.1.1

Before and after the intervention, musculoskeletal ultrasound examinations will be performed using a Siemens Sequoia Silver ultrasound system (probe frequency: 5–12 MHz). The external oblique (EO), internal oblique (IO), transversus abdominis (TrA), and lumbar multifidus muscle (LMM) will be assessed in both groups. For EO, IO, and TrA measurements, the probe will be positioned at the level of the umbilicus along the mid-axillary line. The LMM will be located approximately 2 cm lateral to the L4 spinous process. Muscle thickness will be measured under standardized tasks: active straight-leg raising of the right lower limb in the supine position will be used for EO, IO, and TrA assessment, while single-leg standing on the left lower limb in the upright position will be used for LMM assessment. For each muscle, thickness will be measured three times at rest, at the end of standardized inspiration, and at the end of standardized expiration, and the mean value will be recorded. The muscle activation ratio will be calculated as the ratio of muscle thickness during contraction to that at rest. All measurements will be performed by an experienced sonographer. A subset of measurements will be repeated to assess intra-rater reliability.

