### Statistical analysis

2.11

All statistical analyses will be performed using IBM SPSS Statistics (Version 27.0). Efficacy analyses will follow the intention-to-treat (ITT) principle, including all randomized participants. Continuous variables will be tested for normality and presented as mean ± standard deviation or median (interquartile range), as appropriate, while categorical variables will be expressed as counts and percentages. Baseline characteristics will be summarized descriptively without formal statistical comparisons. Primary and secondary outcomes will be analyzed using linear mixed-effects models, with group, time, and group-by-time interaction as fixed effects and subjects as random effects. Intervention duration (20 vs. 40 min) and baseline values of the outcome measures will be explicitly included as covariates to account for potential confounding effects. Therapist identity will be included as a random intercept to account for potential clustering effects. Model assumptions will be evaluated using residual diagnostics. If significant group-by-time interactions are detected, post-hoc pairwise comparisons with Bonferroni correction will be performed. Missing data will be handled using multiple imputation under the missing-at-random assumption. Safety analyses will include all participants who received at least one treatment, and adverse events will be compared using the chi-square test or Fisher's exact test, as appropriate. Sensitivity analyses, including complete-case analyses, per-protocol analyses, and analyses adjusted for intervention duration, will be conducted to assess the robustness of the primary outcome. All statistical tests will be two-sided, with a significance level set at *P* < 0.05, and 95% confidence intervals will be reported. Effect sizes (e.g., Cohen's d) will also be reported to facilitate interpretation of the clinical relevance of the findings.

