## Discussion

3

To our knowledge, this study is among the first randomized controlled trials to investigate the combined effects of Tuina and core stability training in patients with lumbar disc herniation (LDH). Although both interventions are commonly used in clinical practice, high-quality evidence evaluating their combined efficacy remains limited. Given the high prevalence, prolonged disease course, and increasing trend toward younger onset of LDH, there is a need to explore effective and evidence-based rehabilitation strategies (25, 42). Tuina and core stability training may exert complementary effects, with Tuina primarily improving soft tissue mobility and pain, and core stability training enhancing neuromuscular control and spinal stability (18, 43). The combination may therefore provide complementary and potentially synergistic effects. This integrative approach may address both passive tissue dysfunction and active neuromuscular deficits.

This study has several strengths. It employs a randomized controlled design with blinded outcome assessment and data analysis to minimize potential bias. In addition, multiple outcome measures, including musculoskeletal ultrasound, lumbar imaging, and clinical assessments, are incorporated to comprehensively evaluate changes in lumbar stability and function. Importantly, this study focuses on lumbar stability as a core outcome, which has been insufficiently addressed in previous studies. In addition, the inclusion of a follow-up period allows for the assessment of short-term sustainability of treatment effects.

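### Section 2.11 gates every outcome on a group-by-time interaction that does not fit outcomes with one post-baseline value, and the follow-up claims reach beyond VAS and ODI

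*Protocol article*

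**What the plan says.** **Schedule.** Section 2.1 (Study design) lists three assessment occasions: "Outcome assessments will be conducted at baseline, after 8 weeks of intervention, and at the end of the follow-up period". It adds that the 1-month visit is there to judge short-term maintenance, and names no outcome. Section 2.7 (Outcomes) is specific. It has "primary and secondary outcome measures assessed at baseline and immediately after the intervention", and then says that pain and function "will be reassessed at the 1-month follow-up using the VAS and ODI to evaluate the persistence of treatment effects". Section 2.7.1.1 agrees for the primary outcome: "Before and after the intervention, musculoskeletal ultrasound examinations will be performed". Section 2.7.2.1 gives MRI and X-ray the same before-and-after timing.

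**Analysis.** Section 2.11 (Statistical analysis) analyses primary and secondary outcomes alike with a linear mixed model "with group, time, and group-by-time interaction as fixed effects" and a random subject effect. The baseline value of each outcome also enters as a covariate. Bonferroni-corrected pairwise comparisons follow only if the interaction is significant. No contrast is named as the primary analysis.

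**Claim.** The Discussion lists as a strength that "the inclusion of a follow-up period allows for the assessment of short-term sustainability of treatment effects". The sentence before it presents lumbar stability as the focus of the trial.

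**The concern.** A group-by-time interaction asks whether arms differ in their course over at least two measured times. When baseline is moved to the covariate side and only week 8 remains, there is no course left to compare. Section 2.11 fixes both the baseline covariate and the interaction gate, without saying whether baseline is also a response value. For the primary outcome, the test that opens the door to the pairwise results then either does not exist or is a less efficient analysis than the covariate suggests. The choice between the two would fall to whoever sets up the model.

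The second matter is what the follow-up can show. If only VAS and ODI are collected at 1 month, an unqualified statement about lasting treatment effects, placed beside a sentence on lumbar stability, invites a conclusion for which no data will exist.

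**Working it through.** **1. The plan's own figure.** Inputs from 2.5: effect size 0.78 (read as Cohen's d), two-sided α 0.05, power 0.80, dropout 15%. A two-sample t-test with 27 per arm has noncentrality 0.78 × √(27/2) = 2.87 on 52 df and power 0.803, so 27 reproduces. Dropout: 27 / 0.85 = 31.76, rounded up to 32; 3 × 32 = 96. This calculation uses one two-group comparison at one time and does not depend on the 1-month visit.

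**2. Values available per outcome (2.7, 2.7.1.1, 2.7.2.1).**

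| Outcome | Baseline | Week 8 | 1 month |
|---|---|---|---|
| TrA activation ratio and other ultrasound | yes | yes | no |
| MRI, X-ray | yes | yes | no |
| PBU, JOA, SF-36 | yes | yes | no |
| VAS, ODI | yes | yes | yes |

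**3. Reading A: baseline only as covariate.** For every row but the last, the response has one time level. The interaction has (3−1)(1−1) = 0 df. In the design matrix, intercept (1 column), group (2), time (1) and interaction (2) make 6 columns. The time column equals the intercept and the interaction columns equal the group columns, so the rank is 3. The interaction is not separable from the group effect, and the gate cannot be applied as written.

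**4. Reading B: baseline also in the response.** The interaction has (3−1)(2−1) = 2 df. For subject i in group g, with baseline value Bᵢ:

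Yᵢₜ = μ_g + τt + γ_g·t + βBᵢ + uᵢ + eᵢₜ, t = 0 (baseline), 1 (week 8)

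Yᵢ₁ − Yᵢ₀ = τ + γ_g + (eᵢ₁ − eᵢ₀)

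Both βBᵢ and uᵢ cancel. In complete data the interaction estimate is the difference in mean change, with or without the covariate.

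The printed standard error may still move. With equal variances σ² and baseline-to-week-8 correlation ρ, the subject sum has residual variance σ²(1−ρ²) after adjustment for baseline, while the change has 2σ²(1−ρ). The first is smaller because 1+ρ < 2. The random-intercept variance therefore tends to be fitted at zero and the two variances are pooled. Any smaller standard error from this is not real precision.

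**5. What the alternative gains.** Variance of a pairwise difference with n per arm:

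- change score: 2 × 2σ²(1−ρ)/n
- week-8 value adjusted for baseline: 2 × σ²(1−ρ²)/n (ignoring the small cost of estimating the slope)
- ratio: (1−ρ²) / [2(1−ρ)] = (1+ρ)/2

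The article gives no ρ. For assumed values of 0.3, 0.5 and 0.7 the ratio is 0.65, 0.75 and 0.85.

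**6. Persistence.** Beside the claim "the inclusion of a follow-up period allows for the assessment of short-term sustainability of treatment effects" stands the table in step 2. At 1 month there is no TrA activation, imaging or PBU value. What exists is VAS and ODI, which 2.4.2 describes as impossible to blind and at risk of detection bias.

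**The case against.** **The schedules do not truly conflict.** Section 2.1 lists visits and 2.7 allocates outcomes to them; outcomes of some kind are taken at all three. This stands. A reader might infer that JOA, SF-36 and PBU are left between two schedules, but they are secondary outcomes and 2.7 settles them: baseline and post-treatment, with the 1-month reassessment confined to VAS and ODI. Figure 5, the SPIRIT schedule, is not shown and may say so directly.

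**The primary time point is not open.** This also stands. Ultrasound is done before and after treatment only, so week 8 is the sole candidate. A reader might go further and compare the power of a 2-df interaction test (two visits) with a 4-df test (three visits). That is unsupported: the 4-df test needs 2.1 to override both 2.7 and 2.7.1.1, and its power depends on effect retention and between-visit correlation, which the article does not give. Under assumed values it runs from about 0.60 to 0.97, against 0.71 to 0.84 for the 2-df test, so even the direction is undetermined.

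**Model detail belongs in the SAP.** This is true of what an article leaves out. Here the article states the model, the covariate and the gate, and the combination does not work for the primary outcome.

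**The Discussion never says that stability will be shown to last.** Correct. Pain and disability are treatment effects, 2.7 gives the follow-up that purpose, and 2.4.2 and the Discussion admit the lack of blinding. The statement is too broad, not baseless.

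**Conclusion.** The point holds in two parts.

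- **Analysis.** For the primary outcome and every secondary outcome except VAS and ODI, the gating interaction in 2.11 is either inestimable (0 df) or a change-score contrast that gains nothing from the baseline covariate. Under the second reading, the baseline-adjusted comparison has 65% to 85% of the change-score variance. That range rests on an assumed ρ of 0.3 to 0.7, equal variances at the two visits and complete data. The inestimability under the first reading rests on no assumption beyond the schedule in 2.7.
- **Claim.** The statements on maintenance in 2.1 and on sustainability in the Discussion are supportable only for self-reported, unblinded pain and disability.

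The source of the first part is 2.11, not the difference in wording between 2.1 and 2.7, which calls only for a clarifying phrase. Neither part alters the sample size of 96. The change is worth making before the database is locked and analysis begins.

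**What to change.** 1. **2.11, primary analysis.** Name the week-8 TrA activation ratio, compared between groups with adjustment for its baseline value (ANCOVA type), as the primary analysis. State the pairwise contrasts, keep the Bonferroni correction, and drop the interaction as a precondition.
2. **2.11, other outcomes with one post-baseline value.** Use the same week-8 comparison for imaging, PBU, JOA and SF-36.
3. **2.11, VAS and ODI.** Use a baseline-adjusted repeated-measures model with week 8 and 1 month as response times, and estimate group differences at each visit. In that model the interaction tests only whether the difference shifts between the two visits, so a steady benefit would fail it as a gate.
4. **2.1.** Add that only VAS and ODI are reassessed at 1 month, and check this against Figure 5.
5. **2.1 and Discussion.** Limit the wording on maintenance and sustainability to self-reported pain and disability, noting that these are unblinded.

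The cost is wording in three places. No visits, measurements or participants are added; the claim about lasting effects becomes narrower.
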